### Outcome measurement

#### Primary outcome measure

Antibiotic prescribing rate during the initial consultation (baseline/index consultation, dichotomous scale; number of participants with an antibiotic prescription)

#### Secondary outcome measures based on the complete sample

2.Re-consultation rate at the GP out-of-hours cooperative for the same illness episode within 2 weeks of the initial consultation (within 2 weeks of initial consultation, number of re-consultations)3.(Antibiotic) prescribing rate within 2 weeks of the initial consultation (hence including antibiotic prescriptions during re-consultations) at the GP out-of-hours cooperative (within 2 weeks of initial consultation, dichotomous scale; number of participants with an [antibiotic] prescription)4.(Re-)consultations for fever and fever-related conditions at the GP cooperative during out-of-hours care during the 6-month study period (during complete study period of 6 months, number of consultations and re-consultations)5.Referral to secondary care during the initial consultation and for the same illness episode within 2 weeks of the initial consultation (during index consultation and re-consultations within 2 weeks, number of referrals)

#### Secondary outcome measures based on the telephone survey

6.Parent-reported re-consultation rate at their own GP during routine daytime hours for the same illness episode within 2 weeks of the initial consultation (during telephone survey within 2 weeks of initial consultation, number of self-reported re-consultations)7.Parent-reported antibiotic prescribing during re-consultations at their own GP during routine daytime hours for the same illness episode within 2 weeks of the initial consultation (during telephone survey within 2 weeks of initial consultation, dichotomous scale; number of self-reported [antibiotic] prescriptions)8.Parent-reported hospital admission for that illness episode within 2 weeks of the initial consultation (during telephone survey within 2 weeks of initial consultation, dichotomous scale; number of self-reported hospital admissions)9.Parent-reported satisfaction with care and with provision of written informational materials (during telephone survey within 2 weeks of initial consultation, dichotomous scale and visual analogue scale [VAS] score 1–10 on reassurance and satisfaction with care)10.Parent-reported intention to re-consult the out-of-hours GP centre for a future, similar illness episode (during telephone survey within 2 weeks of initial consultation, dichotomous scale; number of parents with intention to re-consult for a future, similar illness)

### Data collection

During the complete study period from November 2015 to May 2016, we will collect anonymised data on baseline characteristics, antibiotic prescriptions, consultation rates and direct referrals to secondary care for febrile children from GP out-of-hours centre databases (Table 1). This is the complete study sample. Every time the GP processes patient information for a consultation of a child younger than 12 years of age, a pop-up screen will be displayed. GPs then have to answer the question, ‘Did this child have a fever (at home or at the GP cooperative)?’ (yes/no). The International Classification of Primary Care coding system will be used to map reasons for consultation. GPs in the intervention group will receive an additional pop-up after completing the consultation, to check whether or not they handed out the booklet. Because the primary outcome data will be collected in a coded, automatic manner and will be supplied by an independent party that is responsible for the electronic patient file software, there will be no data monitoring committee.

Data on secondary outcomes will be collected for a subsample using telephone surveys during three 2-week periods (Table 1). This will include parents of children also included in the main study. A triage nurse will provide parents with information about the study during their visits in these weeks. If parents give their consent, they will be asked to participate in a telephone survey 2 weeks after the initial consultation. Telephone surveys will be used to question parents about intention to re-consult in the same fever episode and in the future (yes/no), if they received and used antibiotics at re-consultation (yes/no), parental satisfaction (VAS scale), parental reassurance (reassured/not reassured and VAS scale), self-reported complications such as hospital admissions, consultations with their own GP before and after the out-of-hours consultation, and their opinion about the booklet (VAS scale, intention to use again, most important section). Measurements will take place during months 2, 4 and 6. The telephone survey data on secondary outcomes will be entered into a Microsoft Access database (Microsoft, Redmond, WA, USA) by two researchers independently.

### Analysis

First, the data will be processed with IBM SPSS Statistics for Windows software (IBM, Armonk, NY, USA), using mainly descriptive statistics to summarise the data. Second, statistical analysis will be based on the intention-to-treat principle by fitting two-level (GP out-of-hours cooperative and patient) random intercept logistic regression models using MLwiN software. Fixed parameters will be group (intervention vs. control) and size (small vs. large cooperative). The clustering in the data will be accounted for by a random intercept at the GP cooperative level. Additional analysis adjusting for compliance will also be performed (access to booklet vs. actual use). During data analysis, researchers will be blinded to the group assignments.

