The primary outcome is the antibiotic prescribing rate during the initial consultation (dichotomous). The required number of clusters and participants was based on the following assumptions: (1) intra-cluster correlation coefficient (ICC) of 0.01, based on a study that describes the distribution of intra-class correlation coefficients with reference to research in primary care [20]; (2) alpha of 0.05, power of 0.80; (3) proportion of antibiotic prescriptions in the control group of 25% and a proportion of 19% in the intervention group (6% minimal clinical relevant difference), based on the fact that we would thereby reduce the number of children receiving an antibiotic prescription from one in four to one in five to six; and (4) 10% loss to follow-up and 10% efficiency loss based on unequal cluster sizes [21]. We estimated we would need to include 1000 children per cluster (GP out-of-hours cooperative) within 6 months, resulting in a need for 20 clusters to acquire the same power as an individual RCT (with an effective sample size of 737 patients in both the intervention and control groups; 1474 in total). Hence, the total recruitment target for this cluster RCT is 20.000 children recruited at 20 GP out-of-hours centres (10 control, 10 intervention). The chosen reduction in antibiotic prescribing of 6% is arbitrary, and one could consider that any reduction in antibiotic prescribing that results from a low-cost, easy-to-implement intervention is clinically relevant in an era of rising antibiotic resistance.

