**Table 1 Tab1:**
[figure not shown]
Overview implementation booklet using a cluster randomised controlled trial according to Standard Protocol Items: Recommendations for Interventional Trials (SPIRIT) guidelines

*Green* represents the control groups and *blue* the intervention groups. Baseline measurements will take place before implementation of the intervention. Measurement of the primary outcome and secondary outcomes based on the complete sample will go on automatically during the complete study period. The O represents a period of 2 weeks during which data on secondary outcomes based on the telephone survey will be collected

All cooperatives that will be recruited have to be working with the software system that will be used for data collection (Call Manager; Labelsoft Clinical IT B.V., CompuGroup Medical AG, Phoenix, AZ, USA). We will further specifically recruit cooperatives based on (1) their geographical location in The Netherlands to ensure widespread recruitment across the country and (2) the socio-economic status of the community in which they are providing care, to ensure that the sample will be representative of the rest of the country.

The booklet will be used during consultations with febrile children at the GP out-of-hours cooperative. The child’s symptoms will determine which information and advice parents receive from the GP. Inclusion criteria are age between 3 months and 12 years *and* the GP deciding this is a fever-related consult. The child’s temperature has to be measured by parents in advance of the consultation or by GPs during consultations. We specifically choose a subjective term for fever and not a temperature cut-off point, because parents’ considering their child to have a fever is, in our opinion, just as important as an actual clinical fever in light of the illness-focused intervention in this study.

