The average antibiotic prescription rate found in our cohort study, which is chosen as the baseline antibiotic prescribing proportion, is less than the 35% antibiotic prescription rate found in previous studies in adults and children [5, 14, 27]. As we know from previous studies, antibiotic prescription rates vary extensively between GPs. Therefore, we have purposefully chosen to use broad inclusion criteria and not to select specific causes of fever in children. By doing so, we aim to get as close as possible to actual practice and considerations of GPs’ prescribing decisions. This means that we expect that not every child in the intervention group will receive the booklet, owing to various realistic reasons such as a language barrier, a specific disease that is not described in the booklet, or because parents simply do not wish to receive the booklet. Moreover, GPs will differ in their own perceived need to use such an interactive booklet during consultations. While some may use it in all their consultations for children with fever, some may never use it. This probably reflects the use of current information materials, mostly patient leaflets [13]. We choose to perform a pragmatic study, allowing for this variation but also facilitating possible future implementation in daily practice.

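### The primary model makes no use of each cooperative's antibiotic prescribing before implementation, which gives up precision that a 20-cluster trial could recover cheaply

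*Protocol article*

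**What the plan says.** The Analysis section of the protocol article sets out a two-level logistic model and names its fixed terms: "Fixed parameters will be group (intervention vs. control) and size (small vs. large cooperative"). It adds: "The clustering in the data will be accounted for by a random intercept at the GP cooperative level". The Randomisation section stratifies on size alone, so prior prescribing is used in neither the allocation nor the model.

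The note to Table 1, in the Recruitment section, says: "Baseline measurements will take place before implementation of the intervention". It does not say what is measured. The next sentence concerns outcome capture: "Measurement of the primary outcome and secondary outcomes based on the complete sample will go on automatically during the complete study period". Under Outcome measurement, the word baseline is attached to the index visit itself: "baseline/index consultation, dichotomous scale; number of participants with an antibiotic prescription". The Data collection section gathers baseline characteristics and prescriptions over the study period and defines no pre-implementation prescribing rate.

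The Recruitment section requires every cooperative to use the same software and has an independent software party supply coded data automatically.

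**The concern.** There are 10 cooperatives per arm and about 1000 children in each, so the precision of the treatment comparison is governed almost entirely by how much cooperatives differ in their prescribing. A covariate that predicts a cooperative's prescribing removes part of that variation from the standard error, and the cooperative's own earlier rate is a natural candidate. Size, the only covariate planned, may predict prescribing poorly; the article gives no figure either way.

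Two things are at stake. The first is power for a 6-point difference in a design with none to spare. The second is robustness if the true ICC exceeds the assumed value, which comes from a general study of ICCs in primary care and not from these cooperatives.

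**Working it through.** **Inputs from the Sample size section.** "intra-cluster correlation coefficient (ICC) of 0.01"; "alpha of 0.05, power of 0.80" (taken as two-sided); 25% against 19%; 1000 children per cluster; 10 clusters per arm; 10% loss to follow-up; 10% efficiency loss for unequal cluster sizes.

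**Assumption not in the documents.** r is the correlation between a cooperative's observed baseline rate and its underlying trial-period rate.

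**1. The plan's own figure.** Design effect = 1 + 999 × 0.01 = 10.99. Effective n per arm = 10 × 1000 / 10.99 × 0.9 × 0.9 = 737, as stated. The usual two-proportion formula needs 748 per arm for 80% power; 737 gives 79.5%. The calculation reproduces and takes no credit for baseline adjustment.

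**2. Where the variance lies.** In units of p(1 − p), the variance of a cooperative's rate is 0.01 + 0.99/1000 = 0.01099. The between-cooperative share is 0.01 / 0.01099 = 91%. With unlimited children per cooperative, effective n would be only 10 / 0.01 × 0.81 = 810 per arm, against 737.

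**3. Chance differences between arms.** Between-cooperative SD = √(0.01 × 0.25 × 0.75) = 0.0433, or 4.3 points. The difference between two arms of 10 has SD 0.0433 × √(2/10) = 0.019, or 1.9 points. It exceeds 3 points in about 12% of randomisations, before any reduction from size stratification. This is the same variance as in step 2, not an additional problem.

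**4. Effect of the covariate.** Residual variance = 0.01 × (1 − r²) + 0.00099. Effective n = loss factor × 10 / variance. Power is from a noncentral t with 17 df unadjusted and 16 df adjusted.

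| r (assumed) | Variance | Effective n, unequal-size loss only (0.9) | Power | Effective n, both losses (0.81) | Power |
|---|---|---|---|---|---|
| none | 0.01099 | 819 | 79.1% | 737 | 74.8% |
| 0.3 | 0.01009 | 892 | 82.1% | 803 | 78.0% |
| 0.5 | 0.00849 | 1060 | 88.0% | 954 | 84.5% |
| 0.7 | 0.00609 | 1478 | 95.9% | 1330 | 94.0% |

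Both loss factors are shown because loss to follow-up may matter little for an outcome recorded at the index visit. The calculation works on the proportion scale and approximates the planned logistic model.

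**5. A higher ICC.** If the ICC were 0.02 (assumption), with the unequal-size loss only, power is 52% unadjusted and 78% at r = 0.7.

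**6. How the baseline window limits r.** With b baseline children per cooperative, the reliability of the baseline rate is b / (b + 0.99/0.01) = b / (b + 99), and r is the correlation of the true rates between periods times the square root of that reliability.
- About 40 children (six a day in the pilot, over one week): reliability 40/139 = 0.29, so r is at most √0.29 = 0.54.
- About 320 children: reliability 320/419 = 0.76. If true rates correlate at 0.8 (assumption), r = 0.8 × √0.76 = 0.70.

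**The case against.** The strongest reply is that nothing here is wrong. The model includes the stratification factor and the clustering, the sample size reproduces without baseline adjustment, and the random-intercept standard error already contains chance differences between cooperatives. That stands: a reader might infer bias, or invalid inference, from an imbalance in habitual prescribing, and the documents do not support it.

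A reader might also infer that the trial measures baseline prescribing and then ignores it. That is not established. The note to Table 1 does not say what is measured, the table itself is not shown, the word baseline is used elsewhere for the index visit, and the one-week pilot is described only for consultation rates.

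It is tempting to cite the Discussion, "As we know from previous studies, antibiotic prescription rates vary extensively between GPs", as evidence of wide variation between cooperatives. That sentence concerns individual GPs. The Setting section describes cooperatives of 50 to 200 rotating GPs, over whom much of that variation would average out. The argument here rests on the protocol's ICC instead.

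The size of the gain is open. No between-period correlation is given, r = 0.3 yields only about 3 points of power, and a short window limits r. A baseline sample selected by diagnostic coding also differs from the trial population, which is defined by the GP's answer to the fever pop-up, and a window just before November would miss the winter peak. These points shrink the benefit, but a gain remains at every r examined, after paying for the degree of freedom.

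Finally, further covariates could be left to an analysis plan that is not shown. However, the article does name the fixed terms of the model, so the point addresses a stated choice and not a missing detail.

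**Conclusion.** The point holds as lost precision and robustness, not as an error or bias. The variance split of about 91% between cooperatives follows from the protocol's own ICC and cluster size. It makes a cluster-level baseline covariate the main precision lever left once the number of cooperatives is fixed at 20.

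The benefit is conditional. For r from 0.3 to 0.7 the gain is about 3 to 17 points of power with the unequal-size loss alone, and about 3 to 19 points with both losses. Both r and the baseline window are assumptions. The omission is certain; the size of the gain is not. This is a change worth making because it is cheap, but the validity of the primary analysis does not depend on it.

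**What to change.** Before outcome data are unblinded:

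1. State whether the baseline measurements include each cooperative's antibiotic prescribing, and over what window. If they do not, request one cooperative-level aggregate extraction from the common software.
2. Define the covariate as the pre-implementation antibiotic rate in age-eligible children with fever-related coding, expressed as centred log-odds. State the window: several hundred consultations per cooperative where possible, ideally in a season comparable with the trial period.
3. Prespecify it as a fixed covariate in the primary model beside group and size, and keep the group-and-size model as a sensitivity analysis. Adding the covariate only after an imbalance has been seen would be open to challenge.

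The cost is one extra extraction, one cluster-level degree of freedom (17 to 16), and a coded baseline population that differs somewhat from the pop-up-defined trial population. That mismatch can weaken the correlation and so reduce the gain. An aggregate per cooperative suffices, so the article's statement that data cannot be traced to individual patients is no obstacle.

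### The 80% power figure treats 20 cooperatives as an individually randomised trial: with cluster-level degrees of freedom it is about 75% at the stated effective size (about 79% if the 10% loss is handled differently), and the primary test should name a small-sample reference.

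*Protocol article*

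**What the plan says.** The Sample size section of the protocol article assumes "alpha of 0.05, power of 0.80", a "proportion of antibiotic prescriptions in the control group of 25% and a proportion of 19% in the intervention group", an "intra-cluster correlation coefficient (ICC) of 0.01", "1000 children per cluster (GP out-of-hours cooperative) within 6 months", and "10% loss to follow-up and 10% efficiency loss based on unequal cluster sizes". From these it derives an effective sample size of 737 per arm (1474 in total), "resulting in a need for 20 clusters to acquire the same power as an individual RCT", and a recruitment target of "20.000 children recruited at 20 GP out-of-hours centres (10 control, 10 intervention").

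The Analysis section plans a two-level random-intercept logistic model in MLwiN, by intention to treat, with group and cooperative size as fixed effects. On clustering it says: "The clustering in the data will be accounted for by a random intercept at the GP cooperative level". It gives no estimator, test statistic, reference distribution, degrees of freedom or small-sample correction, and it rules none out.

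**The concern.** Both group and size are cluster-level variables, so the treatment effect is estimated between 20 cooperatives, with 17 residual degrees of freedom. A design effect inflates the variance for clustering. It does not account for the between-cluster variance being estimated from few units. A random intercept does not settle this by itself either, because the result depends on how the variance is estimated and what the test statistic is compared with.

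Two things are at stake for the primary outcome. The power statement uses a reference distribution that suits many independent patients, so it is too favourable for 20 clusters. And if the same normal reference were carried into the analysis, the test would reject a true null more often than 5% of the time and the 95% interval would be too narrow.

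**Working it through.** **Inputs (Sample size and Analysis sections).** Rates 0.25 and 0.19; alpha 0.05; ICC 0.01; 1000 children per cluster; 10 clusters per arm; two deductions of 10%; cluster-level fixed parameters intercept, group and size. Sidedness is not stated. Two-sided is assumed because it reproduces the plan: it requires 748 per arm (pooled variance) or 744 (unpooled), against 589 one-sided.

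**1. Reproducing 737.**
- Design effect: 1 + (1000 − 1) × 0.01 = 10.99.
- Effective size per arm: 10,000 / 10.99 × 0.9 × 0.9 = 737.0.

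**2. Power at 737 with a normal reference.**
- Variance sum: 0.25 × 0.75 + 0.19 × 0.81 = 0.1875 + 0.1539 = 0.3414.
- Standard error: √(0.3414 / 737) = 0.02152.
- Standardised effect: 0.06 / 0.02152 = 2.788.
- Power: Φ(2.788 − 1.960) = 79.6% (79.5% with pooled variance). This is the plan's 80%.

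**3. Do 20,000 children make the normal reference adequate?** The share of a cluster mean's variance that lies between clusters is 0.01 / (0.01 + 0.99/1000) = 91%. The precision is set by 20 units, not by the number of children.

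**4. Power with cluster-level degrees of freedom.** With 20 − 3 = 17 df the critical value is 2.110 instead of 1.960. Power comes from the noncentral t distribution.

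| Handling of the 10% loss | Effective n per arm | Normal reference | t, 17 df |
|---|---|---|---|
| As in the plan | 10,000/10.99 × 0.81 = 737 | 79.6% | 74.8% |
| Taken from cluster size (m = 900, design effect 9.99) | 9,000/9.99 × 0.9 = 811 | 83.2% | 78.7% |
| Not applied | 10,000/10.99 × 0.9 = 819 | 83.6% | 79.1% |

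With 18 df (group only), the figure at 737 is 75.1%. Reaching 80% by t needs about 833 (18 df) to 839 (17 df) effective patients per arm. Keeping the plan's deductions and clusters of 1000, 11 cooperatives per arm give about 79% and 12 give about 83%.

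**5. Type I error if a normal reference is used without correction.**
- REML-type variance: P(|t| > 1.960) = 6.7% with 17 df and 6.6% with 18 df.
- ML-type variance, too small by about 17/20: P(|t| > 1.960 × √(17/20)) = P(|t| > 1.807) = 8.8% with 17 df. With 18 df it is 7.9%.

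Simulations with 20 clusters, ICC 0.01, a 25% rate in both arms and the size covariate agree. Across runs with equal and unequal cluster sizes they gave 6.4-6.9% for REML with a normal reference, 8.8-9.4% for ML with a normal reference, and 4.7-5.3% for REML with t on 17 df. The cluster-size spread in the unequal runs is an assumption.

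**The case against.** The strongest reply has three parts.

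First, a reader might infer that the plan has a type I error of 7-9%. The article does not support that. It never says that the group effect will be tested by a Wald z-test or fitted by ordinary maximum likelihood, and a journal article may leave both to an analysis plan that is not shown. The random-intercept sentence is correct as far as it goes: it models the unit of randomisation, and the stratification factor is in the model. This part of the reply stands, so the inflation can be stated only conditionally.

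Second, a reader might infer that the trial as designed has 75% power. That figure belongs to the stated 737, which includes a deduction for loss to follow-up. The primary outcome is prescribing at the initial consultation, extracted automatically from the electronic record, so there is little follow-up in which to lose it. Even if 10% were missing, the clusters would be smaller and the design effect would fall too. Either way t-based power is about 79%, roughly one point below target. This also stands.

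Third, the article says openly that effect size, cluster size and ICC are uncertain and calls the 6-point difference arbitrary, so a shortfall of one to five points might be thought immaterial. This stands only in part. Uncertain inputs do not make the calculation right for the inputs chosen, and the equivalence with an individual trial is a stated claim. Nor can leaving the test to another document rescue both figures: at 737 per arm, a normal reference misses the 5% level and a t reference misses 80% power.

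**Conclusion.** The point holds, at moderate severity. On the plan's own inputs, 20 clusters do not deliver the power of an individual trial with 737 per arm: about 75% rather than 80%. The practical shortfall may be nearer one point, because about 79% is available once the loss deduction is handled in either of the other two ways.

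The error-rate part is conditional: about 6.5-7% (REML-type) or 8-9% (ML-type), only if a normal reference is used uncorrected. It is a reason to fix the inference method in writing, not a demonstrated defect of the planned analysis.

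These figures assume two-sided testing, an ICC of 0.01, the plan's 10% allowance for unequal cluster sizes, and 17 cluster-level degrees of freedom. Neither part calls for a different number of cooperatives on this ground alone, which is why this is not a must-fix.

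**What to change.** In the Analysis section, state that the primary model uses restricted (REML-type) variance estimation and that the group effect and its confidence interval are referred to t with 17 degrees of freedom (20 clusters minus intercept, group and size). A cluster-level t-analysis stratified by size is an acceptable equivalent.

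In the Sample size section, replace the equivalence with an individual trial by the t-based power: about 75% at an effective 737 per arm, or about 79% if the loss is taken from cluster size or not applied to the index-consultation outcome. Say which handling is meant.

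The cost is one sentence and one restated figure, with no change to recruitment. The downside is a slightly lower stated power and confidence intervals about 8% wider than REML with a normal reference (2.110 / 1.960 = 1.076).
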